### Randomization and blinding

2.5

After completion of baseline assessments and confirmation of eligibility, participants will be randomly allocated in a 1:1:1 ratio to the non-exercising control group (CON), traditional resistance training group (TR), or rest-redistribution cluster-set resistance training group (CS). The allocation sequence will be generated by an independent researcher who is not involved in participant recruitment, intervention delivery, outcome assessment, or statistical analysis, using a computer-generated permuted-block randomization scheme with variable block sizes. Variable block randomization was selected because the planned sample size is modest and approximate balance across the three groups should be maintained throughout enrolment, while undisclosed variable block sizes reduce the predictability of allocation. Stratification by baseline DASS-21 or PSQI score will not be used, because simultaneous stratification by multiple symptom measures in a small three-arm trial may create sparse strata and increase operational complexity without a clear gain in allocation efficiency. To ensure allocation concealment, group assignments will be placed in sequentially numbered, opaque, sealed envelopes and stored securely by the independent researcher. Study staff responsible for enrolment will confirm eligibility and complete baseline assessments before opening the next envelope in sequence, and these staff will have no prior access to the allocation sequence.

Given the nature of the exercise intervention, participants and exercise supervisors cannot be blinded to group allocation. However, this trial will adopt a single-blind design in which outcome assessors will remain blinded to group assignment throughout the study. Participants will be instructed not to disclose their allocation during outcome assessments, and assessment visits will be scheduled and conducted by staff members who are not involved in intervention supervision. Data will be recorded using coded participant identifiers, and the statistician will perform analyses using masked group labels until completion of the primary analyses. Unblinding will be permissible only when knowledge of group allocation is essential for participant safety or the management of a serious adverse event. Any request for unblinding will be reviewed by the principal investigator, who, if necessary, will obtain the allocation information from the independent researcher responsible for the randomization sequence. If unblinding occurs, only the minimum necessary personnel will be informed, and the reason and timing will be documented in the trial records.

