### Standardization procedures before repeated assessments

2.9

To reduce measurement variability across baseline, week 4, and week 8 assessments, repeated testing will be conducted under standardized conditions whenever feasible (Ward, 2019; Tinsley et al., 2022). Participants will be assessed at approximately the same time of day across visits, by the same assessors, using the same equipment, device settings, and testing order. They will be instructed to avoid vigorous physical activity, alcohol, and non-essential caffeine for 24 h before each assessment visit and to maintain their usual sleep schedule on the preceding night. Menstrual-cycle phase and major academic stressors (eg, examinations) will be recorded at each assessment.

For body composition and blood biomarker assessments, participants will attend the laboratory in the morning after an overnight fast, after bladder voiding, and before any exercise on that day. For strength testing, participants will be asked to refrain from strenuous exercise for at least 48 h before testing and will complete the same standardized warm-up and test procedures at each time point. For actigraphy-based sleep assessment, the same wear instructions, monitoring duration, and scoring procedures will be applied at each assessment point (Ancoli-Israel et al., 2015).

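### Staff who complete the baseline assessments also open the allocation envelope, and the same assessors are to be used at follow-up where feasible, which conflicts with the promise that assessors stay blinded

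*Protocol article*

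**What the plan says.** Three statements in the protocol article bear on this point.

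- **Envelope opening (section 2.5, Randomization and blinding).** "Study staff responsible for enrolment will confirm eligibility and complete baseline assessments before opening the next envelope in sequence". The sentence goes on to say that "these staff will have no prior access to the allocation sequence".
- **Blinding (section 2.5).** Participants and exercise supervisors cannot be blinded, but "this trial will adopt a single-blind design in which outcome assessors will remain blinded to group assignment throughout the study". The one separation of roles stated for assessors is that "assessment visits will be scheduled and conducted by staff members who are not involved in intervention supervision".
- **Same assessors (section 2.9, Standardization procedures before repeated assessments).** "To reduce measurement variability across baseline, week 4, and week 8 assessments, repeated testing will be conducted under standardized conditions whenever feasible". The next sentence adds: "Participants will be assessed at approximately the same time of day across visits, by the same assessors".

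Section 2.11.2.3 (Maximal dynamic strength) also asks that assessor supervision of the 1RM test be held constant across time points.

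**The concern.** Each statement is reasonable by itself. Opening the envelope only after baseline protects concealment, using one assessor throughout reduces measurement noise, and blinding that assessor protects against detection bias. The difficulty comes from combining them. If the baseline assessor opens the envelope and then returns as the week 4 and week 8 assessor, she knows the arm whenever she measures after randomization.

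What is at stake is any outcome in which an assessor's judgement or handling can move the value. A 1RM attempt is accepted or rejected on technique and range of motion, and encouragement can influence the result. Waist and hip circumferences are taken by hand. The description of the trial as single-blind in sections 2.1 and 2.5 also rests on assessor blinding, so the label would be inaccurate for these measurements.

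**Working it through.** The plan gives no figure on this point, so the check is a comparison of who holds which role.

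**Step 1: who learns the allocation.** In section 2.5 one grammatical subject, the enrolment staff, completes the baseline assessments and then opens the envelope. So the baseline assessor is the envelope opener.

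**Step 2: who assesses later.** Section 2.9 wants the same assessors at baseline, week 4 and week 8, whenever feasible. So, where this is achieved, the baseline assessor is also the follow-up assessor.

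**Step 3: combine.** From steps 1 and 2, the follow-up assessor is the envelope opener and knows the arm. That contradicts the statement in section 2.5 that assessors remain blinded throughout.

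**Step 4: does another provision break the chain?**

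| Provision | What it protects | Breaks the chain? |
|---|---|---|
| Enrolment staff cannot see the sequence in advance (2.5) | Concealment before assignment | No; the arm is known once the envelope is open |
| Assessment staff do not supervise training (2.5) | Learning the arm through training contact | No; enrolment and envelope opening are not covered |
| Participants are told not to disclose their arm (2.5) | Learning the arm from the participant | No; the assessor has already read it |
| Coded identifiers (2.5) | Data records | No; the assessor meets the participant in person |
| Sequence generator does no outcome assessment (2.5) | Independence of that one person | No; that person stores the envelopes but is not the one who opens them |

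Nothing in the article bars envelope openers from the week 4 and week 8 assessments.

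**Step 5: which outcomes are exposed.**

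| Outcome | How it is obtained | Exposed? |
|---|---|---|
| DASS-21, PSQI, POMS | Self-report, submitted online through a QR code (2.13.1); participants are unblinded anyway | Largely not |
| hs-CRP, cortisol, serotonin | Assayed by personnel blinded to allocation (2.11.2.5) | Largely not |
| Actigraphy | Algorithm-derived (2.11.2.2), with the same scoring procedures at each visit (2.9) | Little |
| Body composition | Impedance device reading (2.11.2.4) | Little |
| 1RM squat and deadlift | Judged on technique and range of motion (2.11.2.3) | Yes |
| Waist and hip circumference | Manual, mean of two readings (2.11.2.4) | Yes |

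The statistician works with masked labels until the primary analyses are complete (2.5), which does not depend on who opens envelopes.

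**Step 6: upper bound on extent.** 48 participants × 2 follow-up visits = 96 participant-visits, before dropout. This is a ceiling on exposure, not an estimate of bias; the document offers nothing from which to size the bias.

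**The case against.** The strongest reply is that the enrolment staff and the outcome assessors may be different people. The article uses different names for them, and section 2.5 lists recruitment and outcome assessment as separate functions when it describes the independent researcher. The envelope sentence may be meant only to fix the order of events, with the enrolment staff making sure that baseline is finished rather than measuring it themselves. Unblinding is also allowed only for safety reasons, which would make little sense if assessors routinely opened envelopes. Finally, a journal article need not list every delegation of duties.

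This reading is possible, but the text does not state it. The point does not rest on a missing delegation list: it rests on statements that are present and that conflict when taken at their word. If separate people are intended, one clause would settle it.

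Other parts of the reply stand. The same-assessor provision is qualified by feasibility, so it could give way to the blinding rule, and the plan does not force unblinding at every visit. Assessor blinding is not the only masking in the trial, since the assays and the analysis are masked too. Actigraphy should not be listed among the clearly exposed outcomes. Sections 2.12 and 3 treat secondary outcomes as exploratory.

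A reader might infer more than the document supports in two directions. One is that the confirmatory DASS-21 and PSQI results are compromised; because unblinded participants complete these online, the assessor's knowledge has little route into them. The other is that allocation concealment has failed; the sealed, opaque, numbered envelopes and the lack of prior access to the sequence address that, and nothing here contradicts them.

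**Conclusion.** The conflict is real in the current text, and its reach is modest. As written, the person who completes baseline also opens the envelope and is the preferred assessor at weeks 4 and 8, while the article promises blinded assessors and separates them only from training supervision. The effect is confined to squat and deadlift 1RM, waist and hip circumference, and the accuracy of the single-blind label. No confirmatory conclusion changes.

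This rests on two assumptions: that completing the baseline assessments means carrying them out, and that the same-assessor aim is met in practice. If the first is wrong, the flaw is one of wording. To the extent that the second fails, exposure drops below the ceiling of 48 participants at both follow-up visits. The change should be made because the remedy is nearly free.

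**What to change.** In section 2.5, add that nobody who conducts an outcome assessment at any visit may open or see an allocation. Then reassign the envelope step: once the enrolment staff confirm that eligibility and baseline are complete, a person who does no outcome assessment opens the next envelope and tells only the participant and the exercise supervisor. The independent researcher who already stores the envelopes could do this, as could another existing staff member who does not assess. If the first option is taken, the description of that researcher's independence in section 2.5 should mention the added task.

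This keeps both the same-assessor aim of section 2.9 and the blinding promise, and leaves the sample size and analysis unchanged. A narrower alternative is to state that envelope openers do not assess at weeks 4 and 8, but where they also did the baseline measurements this gives up the same-assessor aim.

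The cost is a wording change, one extra communication per participant (48 in all), and the need for the person opening envelopes to be reachable at enrolment. The article does not say whether the independent researcher would be available each time, so the team should check this before choosing.

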### Informed consent

2.6

The trial will be conducted in accordance with the Declaration of Helsinki and applicable institutional ethics requirements (World Medical A, 2013). The study protocol was approved by the Ethics Committee of the Exercise Science Laboratory at Beijing Sport University (no. 2025422H) and prospectively registered with the Chinese Clinical Trial Registry (no. ChiCTR2500110077; registered on September 29, 2025). Eligible participants will receive written and verbal information describing study aims, procedures, potential risks and benefits, confidentiality protections, and their rights. Written informed consent will be obtained before any study-related assessments. Data will be coded and stored on password-protected, encrypted systems accessible only to authorized study personnel. Participants may withdraw at any time without penalty, and any new information that could influence willingness to continue will be communicated promptly to support ongoing informed consent.

If a participant withdraws after randomization, she will not be reassigned to another study arm; her status will be recorded as withdrawn. With permission, we will invite (but not require) a brief exit interview to document reasons for withdrawal and to inform future protocol refinement. Participants who cannot be contacted for the final assessment, regardless of their intervention status, will be recorded as lost to follow-up.

### Intervention

2.7

This is a three-arm, parallel-group trial comparing a non-exercising control group (CON), traditional resistance training (TR), and rest-redistribution cluster-set resistance training (CS). The intervention period will last 8 weeks. TR and CS will complete three supervised training sessions per week (approximately 48–72 h apart). Training exercises will be identical between TR and CS; only set structure and rest allocation will differ. Participants in CON will not participate in any structured resistance-training sessions and will be instructed to maintain their usual lifestyle and physical-activity habits during the study period.

#### Session structure and general procedures

2.7.1

##### Step 1: warm-up exercises

2.7.1.1

Each supervised training session for TR and CS will include: (1) standardized warm-up, (2) resistance training, and (3) standardized cool-down. Coaches will provide standardized technique cues and ensure correct movement execution. Rest intervals will be timed using a stopwatch.

##### Step 2: resistance training

2.7.1.2

Participants in TR and CS will perform the same five exercises in the same order: supine abdominal curl, plank, wall sit, squat, and deadlift. The only planned difference between TR and CS is the set configuration and distribution of rest intervals.

##### Step 3: cool-down

2.7.1.3

After training, participants will complete a standardized 10-min cool-down. A 3–5-min brisk walk will be used to reduce heart rate, followed by static stretching of major muscle groups (hamstrings, quadriceps, gluteals, and calves). Participants will then perform cat–cow and child’s pose stretches to relax the core and lower back. Finally, foam rolling will be applied to commonly tight areas (e.g., quadriceps, iliotibial band, gluteals, hamstrings, and calves) to reduce perceived stiffness and support recovery.

##### Procedures for CON

2.7.1.4

Participants in CON will not attend training sessions. They will be asked to maintain their usual lifestyle, avoid initiating a new structured exercise program, and complete the same outcome assessments as the training groups at baseline, week 4, and week 8. To minimize differential attention and support retention, CON participants will receive the same brief sleep-health education provided at baseline to all participants and will be contacted weekly to record major changes in physical activity, sleep medication use, or health status. After completion of the study, CON participants will be offered access to the supervised resistance-training program if desired.

#### Intervention arms and set-structure definitions

2.7.2

For each exercise, total rest time will be matched at 240 s across groups to improve comparability. The two set structures are defined as follows:

TR (traditional sets): 3 sets per exercise with between-set rest of 120 s (two rest periods per exercise; total rest = 240 s).CS (rest-redistribution cluster sets): each traditional set is partitioned into two clusters. A brief intra-set rest (20 s) is inserted after cluster 1. Between-set rest is reduced to 90 s (two rest periods per exercise; total between-set rest = 180 s). The remaining 60 s rest is reallocated as intra-set rest (3 sets × 20 s intra-set rest per set = 60 s), such that total rest per exercise remains 240 s. The number of micro-sets differs by exercise (Table 1).

**Table 1 tab1:** Resistance-training prescription and set structure by study arm.

Exercise	TR	CS	Total rest
Wall sit	3 × 60 s holds; 120 s rest between sets.	3 sets; each set: 2 × 30 s holds with 20 s intra-set rests; 90 s between sets.	240 s
Plank	3 × 60 s holds; 120 s rest between sets.	3 sets; each set: 2 × 30 s holds with 20 s intra-set rests; 90 s between sets.	
Supine abdominal curl	3 × 12 reps; 120 s rest between sets.	3 sets; each set: clusters 6–6 reps with 20 s intra-set rests; 90 s between sets.	
Squat	3 × 8 reps; 120 s rest between sets.	3 sets; each set: clusters 4–4 reps with 20 s intra-set rests; 90 s between sets.	
Deadlift	3 × 8 reps; 120 s rest between sets.	3 sets; each set: clusters 4–4 reps with 20 s intra-set rests; 90 s between sets.	

#### Load progression and monitoring

2.7.3

Squat and deadlift loads will be prescribed relative to each participant’s baseline one-repetition maximum (1RM) and progressed linearly: 60% 1RM in weeks 1–2, 65% 1RM in weeks 3–4, 67.5% 1RM in weeks 5–6, and 70% 1RM in weeks 7–8. Coaches will record attendance, completion of prescribed sets and rests, and any adverse events at each session. For CON, weekly contacts will record major changes in health status and physical activity. In addition to the standardized external-load prescription, internal training load will be monitored using the session rating of perceived exertion (sRPE) method. Following the standardized cool-down, participants will report a global sRPE using the modified Borg CR-10 scale, and session training load will be calculated as sRPE × session duration (min) and expressed in arbitrary units (Singh et al., 2007).

### Strategies to improve adherence to interventions

2.8

Adherence-support procedures were informed by the COM-B framework, which conceptualizes sustained exercise behavior as dependent on capability, opportunity, and motivation. Within this framework, standardized instruction and technique guidance were intended to support capability, supervised scheduling and follow-up after missed sessions were intended to support opportunity, and sleep-health education, progress feedback, and supportive communication were intended to support motivation. To encourage adherence and minimize attrition, we will: (1) explain participant responsibilities during recruitment and consent and establish open communication channels; (2) provide all participants (including CON) with a brief standardized education session on sleep health and the potential benefits of evidence-based resistance training; (3) monitor training attendance and protocol fidelity weekly in TR and CS, with follow-up contact within 48 h after any unexcused absence; and (4) provide periodic feedback on participation progress and reinforce engagement through supportive communication. For CON, weekly check-ins will focus on retention and documenting potential contamination (e.g., initiation of a new exercise program).

### Standardization procedures before repeated assessments

2.9

To reduce measurement variability across baseline, week 4, and week 8 assessments, repeated testing will be conducted under standardized conditions whenever feasible (Ward, 2019; Tinsley et al., 2022). Participants will be assessed at approximately the same time of day across visits, by the same assessors, using the same equipment, device settings, and testing order. They will be instructed to avoid vigorous physical activity, alcohol, and non-essential caffeine for 24 h before each assessment visit and to maintain their usual sleep schedule on the preceding night. Menstrual-cycle phase and major academic stressors (eg, examinations) will be recorded at each assessment.

For body composition and blood biomarker assessments, participants will attend the laboratory in the morning after an overnight fast, after bladder voiding, and before any exercise on that day. For strength testing, participants will be asked to refrain from strenuous exercise for at least 48 h before testing and will complete the same standardized warm-up and test procedures at each time point. For actigraphy-based sleep assessment, the same wear instructions, monitoring duration, and scoring procedures will be applied at each assessment point (Ancoli-Israel et al., 2015).

### Safety monitoring and adverse event reporting

2.10

This study will employ a prespecified adverse event monitoring framework. Any unfavorable medical event occurring during the study period that is related to study participation or temporally associated with the study intervention will be defined as an adverse event (AE). Events resulting in hospitalization, serious injury, persistent functional impairment, or any other important medical risk will be classified as serious adverse events (SAEs).

In the TR and CS groups, coaches or research staff will proactively inquire about symptoms or discomfort before and after each training session and document any training-related events. In the CON group, changes in health status will be assessed during weekly follow-up contacts. For all AEs, the nature of the event, onset time, duration, severity, management, outcome, and relatedness to the intervention will be recorded. Participants requiring temporary cessation of training or further medical evaluation will suspend participation until reviewed by the principal investigator. Any SAE will be reported promptly in accordance with ethics committee and institutional requirements.

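### Adverse-event counts in TR and CS cannot be read against CON, because both the definition and the way events are sought differ by arm

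*Protocol article*

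**What the plan says.** Section 2.10 sets the definition: an unfavourable event in the study period is an adverse event if it is "related to study participation or temporally associated with the study intervention will be defined as an adverse event (AE". The same section then has relatedness to the intervention recorded for every adverse event.

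For TR and CS, section 2.10 says that coaches or research staff will "proactively inquire about symptoms or discomfort before and after each training session and document any training-related events". Section 2.7.3 has coaches record "any adverse events at each session".

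For CON, the protocol describes the weekly contact in four places:

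- Section 2.10: "In the CON group, changes in health status will be assessed during weekly follow-up contacts".
- Section 2.7.1.4: CON participants "will be contacted weekly to record major changes in physical activity, sleep medication use, or health status".
- Section 2.7.3: "For CON, weekly contacts will record major changes in health status and physical activity".
- Section 2.8: "For CON, weekly check-ins will focus on retention and documenting potential contamination (e.g., initiation of a new exercise program".

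Table 2 follows the same split. Its safety row lists adverse events at each session for TR and CS, but for CON only weekly contacts that record changes. No enquiry common to all three arms is described.

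**The concern.** A control arm is useful for harms because it shows the background rate of illness, injury and distress over the same weeks. That requires the same definition, the same question and the same threshold in each arm. Here all three differ between the training arms and CON.

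Take an ordinary respiratory infection in week 5. In TR or CS it can qualify on timing alone, because training is under way. In CON there is no training for it to coincide with, so it qualifies mainly if someone judges it to be due to taking part in the study. It must also be serious enough to be noted as a major change at a weekly contact that has other main purposes.

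At stake is the adverse-event table by arm. A reader will naturally compare TR and CS with CON, and a difference could arise from the recording rules alone. Events never asked about in CON cannot be recovered at analysis, so this has to be settled before data collection.

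**Working it through.** The protocol gives no figure for harms, so there is none to reproduce. The check has three parts.

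**1. Planned enquiries per participant**

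Inputs: an 8-week intervention period and 3 supervised sessions per week in TR and CS (section 2.7); enquiry before and after each session (section 2.10); weekly contact in CON (sections 2.7.1.4 and 2.10), taken as one contact per week.

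- TR or CS contact days: 8 × 3 = 24.
- TR or CS enquiries: 24 × 2 = 48, with full attendance.
- CON contacts: 8 × 1 = 8.
- Ratio by enquiry: 48 / 8 = 6. Ratio by contact day: 24 / 8 = 3.

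With one common weekly enquiry the ratio would be 8 / 8 = 1.

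**2. Definition, threshold and purpose side by side**

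| | TR and CS | CON |
|---|---|---|
| Routes to being an adverse event | Due to participation, or timing relative to training | Due to participation; the timing route has no clear referent |
| What is asked or noted | Any symptom or discomfort; any adverse event | Changes in health status, limited to major ones in 2.7.1.4 and 2.7.3 |
| Main purpose of the contact | Active safety enquiry around training | Retention and contamination (2.8) |
| Filter on what is written down | Events related to training (2.10) | Major changes |

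Each row differs between the training arms and CON. None differs between TR and CS.

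**3. What unequal detection could do**

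The detection probabilities here are assumptions; the document gives none. If the true event rate is the same in each arm, the apparent rate ratio is

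apparent ratio = (detection in TR/CS) / (detection in CON).

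With 90% detection in TR/CS:

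| Detection in CON | Apparent ratio |
|---|---|
| 90% | 0.9 / 0.9 = 1.0 |
| 70% | 0.9 / 0.7 = 1.29 |
| 50% | 0.9 / 0.5 = 1.8 |
| 30% | 0.9 / 0.3 = 3.0 |

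The instruction to document training-related events in TR and CS pulls the other way. If staff followed it literally and left out unrelated illness, detection there could fall below that in CON. Swapping the second row gives 0.7 / 0.9 = 0.78. The direction is therefore likely, not certain, and the size is unknown.

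**The case against.** The best case for the plan has several parts.

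*No comparison of harms is planned.* Harms are not among the three aims or the listed outcomes, and section 2.12 states no between-arm test. Section 2.10 describes monitoring to protect participants, and enquiry around a training session cannot be mirrored in an arm without sessions. This stands. It limits the point to descriptive tabulation and any reading of it against CON, and the session-level questioning should stay.

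*The definition is wider than it looks.* Its two routes are alternatives, CON participants do take part (blood draws and 1RM tests), and CON follow-up is placed in the safety section, so CON events are evidently meant to be captured. This stands in part: CON events are not excluded outright, but one route still has no clear meaning there. A reader might also infer that unblinded staff decide relatedness; section 2.10 does not say who does.

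*The 6:1 ratio is not a bias.* This stands. It counts questions, two of which fall on the same day. One event asked about twice is still one event, and a weekly contact can cover the whole preceding week.

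*Form content belongs in the full protocol.* This would answer a complaint about missing detail. It does not answer a stated definition and stated procedures that differ by arm.

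*Some information is collected alike in all arms.* A reader might infer from the weekly sleep-medication question, specified for CON only, that such use cannot be compared across arms. The document does not support that. Sleep-medication use is a PSQI component covering the previous month, and Table 2 schedules the PSQI for baseline, week 4 and week 8. Worsening mood is likewise measured in all arms by DASS-21 and POMS.

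**Conclusion.** The point holds in a limited form. Followed as written, the protocol yields adverse-event counts for TR or CS that are not comparable with those for CON, because definition, threshold and frequency of enquiry all differ. The difference in opportunity is 24 contact days against 8, or up to 48 enquiries against 8, assuming full attendance and one CON contact per week.

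Over-counting in the training arms is the likely direction. A reader might go further and infer that their counts will be inflated whatever the truth. The restriction to training-related events in TR and CS rules out that certainty. The ratios of 1.0 to 3.0 in the working are illustrations under assumed detection rates, not estimates.

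TR versus CS shares one definition and one schedule and is unaffected. Sample size, alpha, power and the co-primary analyses do not change. This is an inexpensive improvement to the safety reporting, not a flaw in the efficacy design.

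**What to change.** 1. In section 2.10, define an adverse event as any untoward medical occurrence from randomization to week 8, in every arm and regardless of relatedness. Record relatedness as a separate item.
2. Ask one identical weekly health-status checklist, with the same threshold for recording, in all three arms: at one existing session per week in TR and CS, and at the existing weekly contact in CON. Bring sections 2.7.1.4, 2.7.3 and 2.8 and Table 2 into line with it.
3. Base any by-arm summary of adverse events on that checklist.
4. Keep the enquiry before and after each session in TR and CS, and report events found that way separately, for those two arms only.

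The cost is a change of wording, a short extra form at contacts that already exist, and more minor events logged. No visits are added.
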